## Methods

### Design

To evaluate the impact of ED-initiated palliative care consultation on quality of life, health care utilization, and survival on patients with advanced cancer, we are conducting a patient-level, single center, single blind pilot randomized controlled trial of 125 to 150 participants. The Institutional Review Board at the Icahn School of Medicine at Mount Sinai Hospital approved all study procedures (GCO 08–1234), and every participant provided informed consent.

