### Outcome measures

Outcomes were specified ahead of time, and include the rate and timing of palliative care consultation, quality of life and depression at 12 weeks, health care utilization, and survival. Independent variables are collected via a baseline interview with the patient or obtained from the electronic medical record, and are listed in Table 2. Dependent variables are listed in Table 3. The primary outcomes include rate and timing of palliative care consultation, quality of life and depression at 12 weeks, hospital length of stay, and survival. Secondary outcomes include costs during the index admission, ICU admission and ICU days, and ED revisits and re-hospitalization at 30 and 180 days. Objective outcomes were chosen that could be obtained from a chart or administrative data review to eliminate the possibility of recall bias or differential follow-up rates between the intervention and care-as-usual group.

**Table 2 T2:** Independent variables

**Variable**	**Measurement**	**Source**
Treatment group	Intervention, usual care	Research coordinator
Primary MD status	Full-time faculty/hospitalist, voluntary/private practice	Medical Record
Primary MD specialty	Heme/Onc, general medicine, other	Medical Record
Age	Years	Medical Record
Gender	Female, Male	Medical Record
Race/Ethnicity	Asian, Black, Hispanic Black, Hispanic White, Native American, White, Other	Patient Interview
Religion	Catholic, Protestant, Jewish, Muslim, Buddhist, Other, None	Patient Interview
Cancer diagnosis	Tumor type and stage	Medical Record
Performance status	ECOG Performance Status	Patient Interview
Medical comorbidities	Charlson co-morbidity index	Medical Record
Prior living situation	Home, nursing home, hospice	Patient Interview
Use of formal home care	Yes/no, Type of services, h/week	Patient Interview
Primary caregiver	Name and relationship/none	Patient Interview
Advance directives	Living will, health care proxy, power of attorney for health care/none	Patient Interview
Medical insurance	Medicare, Medicaid, Medicaid/Medicare managed care, Medicare managed care, traditional indemnity, self-pay, other	Administrative database, Medical Record

**Table 3 T3:** Dependent variables

**Variable**	**Measurement/Instrument**	**Source**

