**Primary Dependent Variables**		
Rate and timing of palliative care consultation	Yes/No; Days from enrollment to consultation	Medical Record
Quality of life	FACT-G at 12 weeks	Patient Interview
Depression	PHQ-9 at 12 weeks	Patient Interview
Hospital length of stay	Days during index admission	Medical Record
Survival	Days from enrollment	Medical Record

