### Data collection and management

After the patient is determined to meet inclusion criteria and provides consent, the face-to-face survey is administered in English or Spanish in the ED and takes approximately 15 minutes, depending on responses and interruptions. Research assistants are trained to understand that data collection never interferes with medical care and the interview is stopped for any reason related to their care. The research assistant administers the baseline survey electronically on a table computer using Survey Monkey, an online survey tool. All protected health information is entered into a separate encrypted, password-protected database with only a unique linking identification number to match this information with that entered in Survey Monkey.

The survey includes questions regarding demographics, including gender, race/ethnicity, marital status, income, education, religious affiliation, type of residence, history of an advance directive or designation of a health care proxy, and health insurance; functional status is measured using the Eastern Oncology Cooperative Group score [8]; quality of life measured using the Functional Assessment of Cancer Therapy-General Measure [9]; and the Patient Health Questionnaire-9 [10] is used to screen for depression. Quality of life and depression are measured again at 6 and 12 weeks. The 6-week measurement was added one month into the protocol because a large proportion of our first participants died before the 12-week follow-up.

Six months after the ED visit, outcome data is collected via the electronic medical record and administrative data review using the *Mount Sinai Data Warehouse*. It provides content such as registration data, lab results, medications, radiology reports, procedures, and billing information. For the chart and administrative data review, a codebook was developed, inter-rater reliability was measured, and the research assistant performing chart abstraction was blinded to patient assignment.

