### Analysis

We estimated our sample size based on one of our primary outcomes (time to palliative care) by utilizing data from the palliative care database on consultation in patients with advanced cancer. The baseline mean time to consultation for such patients seen by palliative care was 9 days (SD = 12). We estimated that our intervention would decrease this number by at least 50%, to 4.5 days (estimated SD = 6 days). Calculations employ two-tailed tests (α = 0.05, with β = 0.80). We plan to enroll and randomize at least 140 patients. We expect to have at least 80% power with α = 0.05 (two-sided) to detect clinically meaningful differences in these primary outcome variables with 70 subjects/group.

The primary analysis will be a traditional intention-to-treat that will compare intervention to control subjects on our predetermined primary and secondary outcomes. Two sample *t*-tests, Mann–Whitney, or *χ*^2^ will be used as appropriate depending on whether the outcome is continuous or discrete, and whether it is normally distributed. For the quality of life data, where there is a baseline score, ANCOVA will be used to compare outcomes between the two groups, and patients who die will be excluded from this analysis. A series of secondary analyses will be conducted if there is significant contamination between the intervention and control group. In the first of these sets of analyses, randomization assignment will serve as an instrumental variable and percentage of admissions receiving palliative care will be included as a covariate. We will also compare primary and secondary outcomes per protocol (i.e., patients will be grouped according to whether they received a consultation, rather than on their randomization scheme). We expect outliers in our outcome data and will not be excluding them from the analysis. Because of the small sample size, we will not account for permuted blocked randomization in the analyses.

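### Survival is a primary outcome, but the test rule has no censoring, and deaths are sought only in one hospital's record

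*Protocol article*

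**What the plan says.** All references are to the protocol article.

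- **Outcome measures**: "The primary outcomes include rate and timing of palliative care consultation, quality of life and depression at 12 weeks, hospital length of stay, and survival". The same section argues that outcomes available from chart or administrative review were chosen "to eliminate the possibility of recall bias or differential follow-up rates between the intervention and care-as-usual group".
- **Table 3**: the survival row reads "Survival Days from enrollment Medical Record". It gives no end of follow-up and no second source. The readmission and ED-revisit rows, by contrast, state 30 and 180 days.
- **Data collection and management**: "Six months after the ED visit, outcome data is collected via the electronic medical record and administrative data review". The administrative data come from the same hospital's data warehouse. No external death source is named.
- **Design**: "single center, single blind pilot randomized controlled trial of 125 to 150 participants".
- **Analysis**: the intention-to-treat analysis will "compare intervention to control subjects on our predetermined primary and secondary outcomes". A t-test, Mann-Whitney or chi-square "will be used as appropriate depending on whether the outcome is continuous or discrete, and whether it is normally distributed". The one exception is ANCOVA for quality of life. Kaplan-Meier, log-rank, Cox, censoring, and a rule for patients alive or of unknown status do not appear.
- **Recruitment**: phone numbers for the patient, friends and family are collected to limit loss to follow-up. No section uses them to establish vital status.

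**The concern.** Days from enrollment to death is a right-censored outcome. Some patients will be alive at six months, and some may have left the hospital's view before then. The Analysis rule chooses a test by data type and normality, neither of which addresses this. It therefore leaves open what value such patients receive, and the test's behavior depends on that choice.

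The second issue is ascertainment. A single hospital's record may not contain deaths at home, in hospice or elsewhere. The Intervention arm section describes transition planning, daily inpatient visits and outpatient palliative referral, all of which can change how much contact a patient has with the hospital. Death capture could therefore differ by arm because of the intervention itself, which is what the Outcome measures section says chart data rule out.

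The stake is the survival estimate. The Discussion hypothesizes a possible survival gain and says that the pilot's estimates will inform a larger multicenter trial.

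**Working it through.** **1. The plan's own figure.** The Analysis section gives time to consultation as 9 days (SD 12) against 4.5 days (SD 6), with 70 per group, two-sided alpha 0.05 and 80% power. The average variance is (12² + 6²)/2 = 90, so n = 2 × 90 × (1.960 + 0.842)² / 4.5² = 69.8, or 70 per group, with power 80.1%. The stated size reproduces. It does not rest on survival, and the article gives no survival assumption (median, event count or hazard ratio), so changing the survival analysis leaves it untouched.

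**2. What the test rule does in different situations.** The simulation used 70 per arm, exponential survival, a cut-off at day 180, and 2,000 trials per setting. The article says only that many early participants died before 12 weeks, so mortality is assumed: median 90 days (75% dead by day 180) or 180 days (50% dead). The Monte Carlo standard error at 0.05 is √(0.05 × 0.95/2000) = 0.005. Each cell gives the rejection rate for median 90 / median 180.

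| Situation | t-test | Mann-Whitney | Chi-square | Log-rank |
|---|---|---|---|---|
| (a) No effect, status complete to day 180 | 0.044 / 0.056 | 0.041 / 0.054 | 0.049 / 0.050 | 0.044 / 0.050 |
| (b) HR 0.70, status complete | 0.378 / 0.248 | 0.392 / 0.293 | 0.393 / 0.286 | 0.427 / 0.296 |
| (c) No effect, 30% control and 10% intervention liable to be last seen early | 0.114 / 0.193 | 0.112 / 0.204 | 0.123 / 0.086 | 0.048 / 0.052 |
| (d) No effect, deaths missed in 10% control and 20% intervention | 0.122 / 0.078 | 0.126 / 0.085 | 0.149 / 0.080 | 0.141 / 0.085 |
| (e) As (d), 10% and 30% | 0.298 / 0.174 | 0.334 / 0.216 | 0.420 / 0.233 | 0.402 / 0.227 |

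In (c) the last-seen day is uniform over 0 to 180 and applies only if it precedes death or the cut-off. The t-test and Mann-Whitney take it as the survival time, chi-square counts the patient as alive, and log-rank censors there. In (d) and (e) a missed death is counted as alive at day 180. With no true effect the arms are interchangeable, so reversing the unequal rates gives the same two-sided rejection rates with the bias pointing the other way.

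A further choice is to compare days only among patients who died. With complete status and HR 0.70, Mann-Whitney then has power 0.094 / 0.055, against 0.392 / 0.293 when everyone is included.

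**3. Size of a spurious mortality gap.** Observed mortality = m × (1 − s × q), where m is true mortality, s the share of deaths outside the hospital and q the share of those unrecorded. Assume m = 0.60 in both arms and q = 0.5, with s = 0.4 in one arm and 0.6 in the other:

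- 0.60 × (1 − 0.4 × 0.5) = 0.48
- 0.60 × (1 − 0.6 × 0.5) = 0.42

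The gap is 6 points. Its standard error is √(0.48 × 0.52/70 + 0.42 × 0.58/70) = 0.084, so the shift is 0.06/0.084 = 0.7 standard errors and the false-positive rate is about 11% rather than 5%. With m from 0.5 to 0.7, s of 0.3 to 0.4 against 0.5 to 0.6, and q from 0.3 to 0.5, the gap runs from 0.5 × (0.5 − 0.4) × 0.3 = 1.5 points to 0.7 × (0.6 − 0.3) × 0.5 = 10.5 points. Its sign depends on which arm has the larger unrecorded share.

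**The case against.** The strongest defense is that the listed tests need not fail. Outcomes are collected at one common time. A patient known to be alive then ranks above every decedent, so Mann-Whitney with ties at day 180, or chi-square on six-month mortality, uses everyone. Rows (a) and (b) bear this out. A reader might infer that the tests are invalid, or that with 60% assumed mortality the 56 survivors of 140 (40%) must be dropped or given arbitrary values. The documents do not support that: harm needs incomplete status or a decedents-only comparison, and the article specifies neither.

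A reader might also infer that missed deaths would lengthen apparent survival in the intervention arm. No passage says that the intervention moves deaths out of the hospital. Daily visits and outpatient palliative referral could equally improve death capture in that arm. The direction is unknown.

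There is mitigation too. Interviews at 6 and 12 weeks can reveal deaths, contact numbers are held, and patients planning to leave the area are excluded. But the interviews end well before six months, and neither they nor the contacts are listed as a survival source.

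Finally, this is a condensed article on a pilot, and a fuller plan may state a censoring rule. That lowers the weight of the point but does not remove it. The article fixes a test list for all primary outcomes, makes a specific exception for quality of life, and names one source for survival.

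**Conclusion.** The point holds in a limited form. As written, the Analysis rule sends a right-censored primary outcome to tests that take no account of censoring, and it does not secure the condition under which they are sound, namely known status for every patient to a common day 180.

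- If that condition is met, little is lost: type I error is 0.041 to 0.056, with power a little below log-rank.
- If it is not met, a decedents-only comparison loses most of its power, and using last-seen days as survival times can raise the t-test and Mann-Whitney false-positive rate to 0.11 to 0.20.
- Unequal death capture is possible in either direction. At 10% against 20% missed, the listed tests reject falsely in 0.08 to 0.15 of trials, and log-rank does no better (0.09 to 0.14). The claim that differential follow-up is eliminated is therefore too strong for survival.

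These sizes rest on assumed mortality, loss and missed-death rates; the article quantifies none of them. They show what the open choices could do, not what has happened in this trial.

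**What to change.** 1. **Analysis**: state that survival will be analyzed by Kaplan-Meier and log-rank, censoring at the date last known alive or at day 180, whichever is earlier. A Cox model adjusted for baseline ECOG status is optional. Cancer type should enter only in a few prespecified groups, since Table 1 has 27 rows for about 140 patients.
2. **Data collection and management, and Table 3**: add confirmation of vital status at day 180, done identically in both arms by staff blind to assignment, using the patient, family and friend contacts already collected and, if available, a death-index match. This step is needed in its own right, because a time-to-event method handles censoring but not unrecorded deaths.
3. **Outcome measures**: soften the claim, for example by saying that chart and administrative outcomes reduce differential follow-up, with survival subject to a separate vital-status check.

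The cost is a few sentences plus a few hours of calls or a small matching fee. The sample size does not change, and the article reports that enrollment was still under way at submission.

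### ANCOVA is fixed only for quality of life, so read literally 12-week PHQ-9, a primary outcome with its own baseline score, gets an unadjusted test and loses efficiency

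*Protocol article*

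**What the plan says.** The Analysis section sets an intention-to-treat comparison of the two groups by t-test, Mann–Whitney or chi-square, chosen by the type and distribution of the outcome. It then makes one exception: "For the quality of life data, where there is a baseline score, ANCOVA will be used to compare outcomes between the two groups". The same sentence leaves patients who die out of that analysis.

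Under Outcome measures, the text and Table 3 list quality of life (FACT-G at 12 weeks) and depression (PHQ-9 at 12 weeks) as two separate primary outcomes. Data collection and management puts FACT-G, PHQ-9 and functional status in the baseline survey and adds: "Quality of life and depression are measured again at 6 and 12 weeks". It also explains that the 6-week measurement was introduced because many of the first participants had died before week 12.

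On other baseline data, Outcome measures states: "Independent variables are collected via a baseline interview with the patient or obtained from the electronic medical record". Table 2 includes "ECOG Performance Status" among them. The Analysis section gives none of the Table 2 patient characteristics a role. The only other covariate it names, receipt of palliative care in the instrumental-variable analysis, arises after randomization.

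**The concern.** The plan justifies ANCOVA by the existence of a baseline score. PHQ-9 has one as well, collected in the same interview and on the same schedule as FACT-G. Two primary outcomes of the same kind would therefore be analysed differently, and no reason is given.

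Two things are at stake. First, efficiency: an unadjusted comparison leaves in the residual the part of the 12-week score that baseline PHQ-9 already explains. That loss falls where data are likely to be scarcest, because a 12-week interview needs a living patient. Second, clarity: if the words on quality-of-life data were meant to cover both scales, the text does not say so. The model for a primary outcome could then be settled after the data are seen. The Discussion intends the pilot's effect estimates to inform a larger multicenter trial, so avoidable imprecision would carry forward.

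**Working it through.** **1. The plan's own figure.** Inputs from the Analysis section:
- "Calculations employ two-tailed tests (α = 0.05, with β = 0.80"; the 0.80 is read as power.
- Control group: "The baseline mean time to consultation for such patients seen by palliative care was 9 days (SD = 12" (days).
- Intervention group: "to 4.5 days (estimated SD = 6 days".
- "We plan to enroll and randomize at least 140 patients", that is, 70 per group.

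With unequal SDs, n per group = (12² + 6²)(1.960 + 0.842)² / 4.5² = 180 × 7.849 / 20.25 = 69.8, so 70. Power at 70 per group is 80.1% by the normal approximation and 79.6% by the noncentral t. The stated figure is reproduced. It rests on time to consultation with an unadjusted test, so the present point does not touch it.

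**2. What baseline adjustment is worth for PHQ-9.** Let r be the within-group correlation between baseline and 12-week PHQ-9. The documents do not give it, so the values below are assumptions.
- Residual variance factor: 1 − r²
- Gain in effective sample: 1/(1 − r²)
- Power, at the difference that has 80% power unadjusted: Φ[(1.960 + 0.842)/√(1 − r²) − 1.960]
- Detectable difference in SD units with n per group: 2.802 × √(2/n) × √(1 − r²)

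| r (assumed) | variance factor | sample gain | power | effective n, from 70 | detectable difference, n = 70 | effective n, from 35 | detectable difference, n = 35 |
|---|---|---|---|---|---|---|---|
| 0 | 1.00 | 1.00 | 80.0% | 70 | 0.474 | 35 | 0.670 |
| 0.3 | 0.91 | 1.10 | 83.6% | 77 | 0.452 | 38 | 0.639 |
| 0.5 | 0.75 | 1.33 | 89.9% | 93 | 0.410 | 47 | 0.580 |
| 0.6 | 0.64 | 1.56 | 93.8% | 109 | 0.379 | 55 | 0.536 |

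The 35 per group is an illustrative assumption for heavy loss to death; the article gives no number. The table compares ANCOVA with a t-test on means. Against Mann–Whitney the figures are only a guide. The price is one residual degree of freedom: 138 to 137 with 70 per group, 68 to 67 with 35.

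**3. ECOG and survival.** A simulation of 140 patients (1,500 runs) used assumed values throughout: median survival about 150 days, censoring at 180 days, conditional hazard ratio 0.6, ECOG spread over levels 0 to 4.

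| assumed log hazard ratio per ECOG level | power without / with ECOG | mean log hazard ratio | mean standard error |
|---|---|---|---|
| 0.2 | 53.6% / 54.5% | −0.509 / −0.520 | 0.2498 / 0.2511 |
| 0.4 | 50.0% / 56.3% | −0.476 / −0.517 | 0.2477 / 0.2494 |
| 0.6 | 42.4% / 54.4% | −0.432 / −0.508 | 0.2452 / 0.2478 |

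The standard error does not fall. Power rises because the conditional log hazard ratio is further from zero than the marginal one. The gain runs from about 1 to 12 points. Simulation error on each power figure is about √(0.25/1500) = 1.3 points, so the first row shows little beyond noise.

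**The case against.** The best defence is that the words on quality-of-life data are a loose label for both interview scales. The Abstract and Background put quality of life and depression in one outcome item, with FACT-G and PHQ-9 named together. The ANCOVA sentence does not name FACT-G. It also carries the only rule for patients who die, which a 12-week PHQ-9 comparison needs just as much. This reading is possible. It sits badly with Table 3, which gives the two outcomes separate rows and instruments, and with Data collection and management, which names both when both are meant. Even if it is right, the text needs the missing words.

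It can also be said that this is a condensed article on a pilot, that covariates are commonly left to an analysis plan, and that unadjusted tests are valid under randomization. All of that stands, and it limits the point to lost efficiency on one outcome. It does not remove the point, because the article itself fixes ANCOVA by a reason and then applies it to only one of the two scales that meet it.

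A reader might go further and infer that chance imbalance in ECOG could overwhelm the treatment effect, or that precision is being lost on survival, length of stay and costs. The documents do not support this:
- They state no prognostic strength for ECOG.
- The error rate of an unadjusted test already allows for chance imbalance.
- In a Cox model, adjustment changes the estimand and can raise power, but it does not shrink the standard error.
- For length of stay, assumed correlations with ECOG of 0.1 to 0.3 remove only 1% to 9% of variance (80% power becomes 80.4% to 83.6%). The plan also expects outliers and allows a rank test, to which that linear-model gain may not carry over.

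**Conclusion.** The point holds for depression. Read literally, the plan compares 12-week PHQ-9 without its baseline, although its own reason for ANCOVA applies. The loss is equivalent to forgoing about 10%, 33% or 56% more patients at assumed correlations of 0.3, 0.5 or 0.6. The true size cannot be derived from the documents.

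Choosing the unadjusted test introduces no bias, and the 70 per group is unaffected. Comparing only survivors is a separate matter, which baseline adjustment does not cure. For survival, adjustment for ECOG is an optional refinement: any gain is in power, for a conditional hazard ratio, and depends on an assumed prognostic strength. Nothing in the documents supports requiring ECOG adjustment of length of stay or costs.

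**What to change.** In the Analysis section, state that 12-week PHQ-9 is compared between groups by ANCOVA with baseline PHQ-9 as covariate, as FACT-G is with its own baseline, and that the unadjusted comparison is kept as a sensitivity analysis. Naming both instruments in that sentence also settles whether its rule on patients who die covers PHQ-9. Cost: one sentence, one degree of freedom, no new data. At submission the trial was still enrolling, so the change could be made before analysis.

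Optional and secondary: pre-specify baseline ECOG as a covariate in a time-to-event model for survival. The tests listed in the article include no such model, so it would have to be named. Say that the target is then a conditional hazard ratio and that any gain is in power, not in a smaller standard error. Cost: one or two further degrees of freedom.

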## Discussion

Here, we describe the design of a clinical trial to determine the impact of a palliative care intervention for advanced cancer patients in the ED on quality of life, depression, health care utilization, and survival. While this is a pilot trial to establish feasibility, it will provide an estimate of the effect of the intervention on our predetermined outcomes that can be used to inform the design of a larger multicenter trial.

Systematic reviews of palliative care have concluded that trials are sparse and findings limited due to methodological shortcomings inherent to this patient population [11]. Only a small proportion of the research in palliative care is based on clinical trials [12], as recruitment and retention of these patients for palliative care studies have proven challenging [13]. The ED setting adds other unique challenges not encountered in other settings. The environment is crowded and chaotic, and there is little privacy. Patients often have a high symptom burden and are in significant distress, all of which can preclude participation in research. The specificity of our environment, coupled with the lack of published clinical trials in palliative care, make the publication of our study protocol especially important to further research in this arena.

Visits to the ED for patients with advanced cancer are common, demonstrating the potential for altering the clinical course of these patients in this setting [14,15]. Despite this, there has been almost no needs-based research in palliative care and emergency medicine, and until recently little emphasis has been placed on education, research, or practice guidelines in end-of-life or palliative care in this important setting [16]. While some EDs are pilot testing palliative care programs, there has not been a structured and rigorous approach to the development and testing of such interventions to assure their success and test their impact on predetermined outcomes.

We hypothesize that ED-initiated palliative care consultation will increase the rate and decrease time to palliative care consultation, improve quality of physical and mental health, decrease health care utilization, and may even increase survival. We believe that it is not only feasible to enroll ED patients with serious illness in trials of palliative care, but that the ED presents a unique window in which to do so.

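### The 12-week FACT-G comparison, a primary outcome, leaves out patients who die, so it compares survivors and could be biased if mortality differs between arms

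*Protocol article*

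**What the plan says.** The Outcome measures section makes quality of life and survival primary together: "The primary outcomes include rate and timing of palliative care consultation, quality of life and depression at 12 weeks, hospital length of stay, and survival". Table 3 fixes the quality-of-life measure as FACT-G at 12 weeks.

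The Analysis section opens its description of the comparisons with "The primary analysis will be a traditional intention-to-treat that will compare intervention to control subjects on our predetermined primary and secondary outcomes". Two sentences later it gives the rule for quality of life: "ANCOVA will be used to compare outcomes between the two groups, and patients who die will be excluded from this analysis". The rule has no time limit, although Data collection and management places the chart review at six months. It names the quality-of-life data only; PHQ-9 also has a baseline score and is not mentioned.

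Data collection and management explains that the 6-week measurement was added because "a large proportion of our first participants died before the 12-week follow-up". The article gives the 6-week score no stated role in the primary comparison. The Discussion hypothesises that the intervention will "decrease health care utilization, and may even increase survival".

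**The concern.** Death by 12 weeks happens after randomisation. Once patients who die are removed, the two groups are no longer the groups that randomisation made comparable. If the intervention keeps some frailer patients alive, they enter its FACT-G mean and pull it down, while their counterparts in the control arm have died and are not counted. If it shortened life among the frail, its mean would rise. Either way the survivors' difference can depart from zero with no effect on any patient's quality of life. Adjustment for baseline FACT-G removes only the part of the selection that the baseline score captures.

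The plan conditions one primary outcome on being alive while treating survival as another primary outcome that the intervention might change. The Discussion says the estimates will inform a larger multicentre trial, so a survivor-selected estimate could be carried forward.

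**Working it through.** **1. The plan's own sample size.** Inputs from the Analysis section: means 9 and 4.5 days, SDs 12 and 6, two-sided α = 0.05. The 0.80 that the plan prints as β is read as power.

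- Pooled SD = √((12² + 6²)/2) = √90 = 9.487.
- n per group = 2 × (9.487 × (1.960 + 0.842)/4.5)² = 69.8, rounded up to 70. This reproduces the plan's figure.
- The standardised difference is 4.5/9.487 = 0.474.

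This calculation is for time to consultation with every randomised patient counted. It does not address FACT-G among survivors.

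**2. How many patients remain.** The document gives no death rate, so 12-week mortality m is assumed, equal in both arms. Survivors per arm: k = 70 × (1 − m). Power at 0.474 SD: Φ(0.474 × √(k/2) − 1.960). No FACT-G effect size is stated, so 0.474 only carries over the planned standardised difference, and any gain from baseline adjustment is ignored.

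| m | k per arm | Power |
|---|---|---|
| 0% | 70 | 80% |
| 30% | 49 | 65% |
| 50% | 35 | 51% |

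**3. Bias with no true effect, closed form.** Assumptions: a latent health score f is standard normal; a patient dies by 12 weeks if f falls below the cut c for that arm's mortality p; FACT-G, in SD units of the score left after baseline is accounted for, has correlation ρ with f. The mean of f among survivors is φ(c)/(1 − p):

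- p = 50%: 0.3989/0.5 = 0.798
- p = 40%: 0.3863/0.6 = 0.644
- p = 30%: 0.3477/0.7 = 0.497

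Bias (intervention minus control) = ρ × (intervention survivor mean − control survivor mean).

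| Control / intervention mortality | Difference in mean f | ρ = 0.3 | ρ = 0.5 | ρ = 0.7 |
|---|---|---|---|---|
| 50% / 40% | 0.644 − 0.798 = −0.154 | −0.046 | −0.077 | −0.108 |
| 50% / 30% | 0.497 − 0.798 = −0.301 | −0.090 | −0.151 | −0.211 |
| 50% / 50% | 0 | 0 | 0 | 0 |

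If the 50%/40% rates are exchanged, so that the intervention arm has the higher mortality, the signs reverse and the survivors' comparison favours the intervention by 0.05 to 0.11 SD.

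**4. The same with baseline in the model.** A large-sample simulation fitted the ANCOVA to survivors, assuming a baseline-to-12-week correlation of 0.5, a correlation of 0.3 to 0.7 between latent health and 12-week FACT-G, and no true effect. Bias is in SDs of 12-week FACT-G. Type I error is for 70 randomised per arm at a nominal 5%.

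| Control / intervention mortality | Bias (SD) | Type I error |
|---|---|---|
| 30% / 30% | about 0 | 5.0% |
| 40% / 30% | −0.03 to −0.09 | 5.3% to 8.2% |
| 50% / 40% | −0.04 to −0.09 | 5.4% to 8.0% |
| 50% / 30% | −0.07 to −0.17 | 6.6% to 17.1% |

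Baseline adjustment reduces the bias but does not remove it.

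**The case against.** Quality of life has no value after death, so a survivors' analysis answers a sensible question and the article discloses it openly. Survival is compared separately as a primary outcome, so a survival harm would not go unexamined, and a 6-week score was added because of early deaths. This is a single-centre pilot sized on time to consultation. All of that stands, and it is a reason to keep the ANCOVA. None of it changes what the ANCOVA estimates: neither the survival comparison nor the 6-week score is tied to the FACT-G result.

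Several stronger readings are tempting, and the document does not support them:

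- *The plan predicts a survival difference and high mortality.* The Discussion says only that survival may increase. The remark on early deaths concerns the first participants, about one month in, and gives no rate.
- *The exclusion flatly contradicts intention-to-treat.* The article contrasts intention-to-treat with grouping patients by consultation received. In that sense the ANCOVA does analyse patients as assigned. The supportable statement is that the label covers an analysis that omits some randomised patients.
- *A survival harm would show up as a quality-of-life benefit.* It could. At 50% versus 40%, 35 and 42 patients remain, the standard error is about √(1/35 + 1/42) = 0.229 SD, and the step 3 bias is roughly 0.2 to 0.5 of that.
- *Worst-rank must become the primary test.* Placing death below every living score is one choice among several and is contestable in palliative care. If mortality were near half, survival could dominate the result.

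**Conclusion.** The point holds as a structural one. The stated rule compares a primary outcome between survivors, who are not protected by randomisation, under an intention-to-treat heading, and nothing else in the article repairs this.

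The size is conditional. It rests on assumed mortality, assumed correlations, and death modelled as a sharp cut on latent health, which is the strongest form of selection. A 20-point mortality difference with strong correlation distorts the result seriously, a 10-point difference does so modestly, and equal mortality with the same selection leaves only the loss of numbers. The document cannot say which of these applies.

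**What to change.** Change the Analysis text as follows:

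1. State that the survivors-only ANCOVA estimates a difference conditional on being alive at 12 weeks, and do not describe it as intention-to-treat on all randomised patients.
2. Limit the exclusion to deaths before the 12-week assessment. Read literally, the present wording could also drop a patient who gave a 12-week score and died later.
3. Report the number of deaths by arm beside the ANCOVA result.
4. Pre-specify an analysis of FACT-G in all randomised patients that accounts for death, for example a worst-rank Wilcoxon test or a baseline-adjusted ordinal regression with death as the lowest category. Read any claim of quality-of-life benefit together with it.
5. State whether the same handling applies to PHQ-9.

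The cost is a few sentences and one extra analysis on data already being collected. Enrolment was still open when the article was submitted. The downside is that the composite mixes death with quality of life and may be driven by survival, so both components must be shown.
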